### 2.9 Recruitment

We will approach potential participants in the community via interactive face-to-face campaigns, public activities (e.g., interactive workshops/campaigns) across the territory, and advertisements in local newspapers and social media. Interested individuals will be invited to complete an online assessment to confirm eligibility.

### 2.10 Sequence generation

Randomization of the sequence of initiation in 18 districts will be conducted 4 weeks prior to the commencement of study by an independent researcher (IR) not involved in assessment or delivery of the intervention. All 18 districts will receive no interventions in the first 4 weeks. After the first 4 weeks, 4-6 districts will initiate the stepped-care CMH intervention and this procedure continues at 4-week intervals, until all 18 districts cross over to the intervention phase.

### 2.11 Concealment mechanism

The computer-generated randomized allocation sequence that determines the chronological sequence of initiating the intervention will be securely kept in opaque sealed envelopes by the investigator who will not interact with the participants during recruitment, allocation, or interventions. Project coordinators will contact the IR to retrieve the allocation sequence before the commencement of the intervention. The allocation sequence will be generated by the IR who is not involved in the assessment or delivery of the intervention. This investigator’s sole responsibility is to perform randomization in accordance with the study protocol. Screeners will enroll participants, but they will not have access to this list.

### 2.12 Blinding

Blinding of participants is not feasible for this trial due to the nature of the interventions. The research personnel responsible for delivering the CHM intervention cannot be blinded either. To mitigate potential bias, the clinician-rated TCM body constitution assessment and all objective outcomes, including data from wearable devices and the collection of biological samples, will be conducted by research personnel who are blinded to both the study design and participant group allocation. These assessors will have no role in delivering the intervention, and all participants will be instructed to conceal their allocation status during these assessments.

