**Level 2: Standardized CHM intervention**

The Level 2 intervention, employing a higher-intensity formula consisting of 5 to 11 herbs, is designed for participants experiencing moderate symptoms of depression, anxiety, and insomnia, defined by a PHQ-9 score ranging from 10 to 19, a GAD-7 score from 10 to 14, or an ISI score from 15 to 21. A Chinese medicine practitioner will prescribe the herbal formula based on the participant’s TCM syndrome. The Level 2 intervention includes three types of herbal formulas for excess syndrome, deficiency syndrome and deficiency-excess complex syndrome, respectively. The classification of these three syndromes will primarily rely on the clinical judgment of the Chinese medicine practitioner, who will consider the patients’ symptoms, signs, and other body constitutional characteristics. Importantly, all herbal formulas are standardized, which facilitates the evaluation of their effectiveness and allows for easy replication in future studies. Details of the three formulas are listed in
Table 2. The level 2 CHM intervention will last for 6 weeks, where participants will be instructed to take the herbal formula twice a day. Participants whose symptoms do not downgrade to mild level in their assessment score after level 2 intervention will be stepped up to receive the level 3 intervention, while other participants who downgrade to mild/minimal symptoms will be followed up for another 6 weeks to examine the short-term effects of the herbal formula intervention.

**Table 2. T2:** The composition of the herbal formulas (Level 2 intervention).

	Name	Ingredients	g/day
Excess syndrome	Jia Wei Xiao Yao San	Bupleuri Radix, Angelicae Sinensis Radix, Paeoniae Radix Alba, Atractylodis Macrocephalae Rhizoma, Poria, Glycyrrhizae Radix et Rhizoma, Moutan Cortex, Gardeniae Fructus	10
Deficiency syndrome	Gui Pi Tang	Ginseng Radix et Rhizoma, Jujubae Fructus, Ziziphi Spinosae Semen, Glycyrrhizae Radix et Rhizoma, Polygalae Radix, Zingiberis Rhizoma Recens, Angelicae Sinensis Radix, Atractylodis Macrocephalae Rhizoma, Poria cum Radix Pini, Astragali Radix, Longan Arillus	10
Deficiency-excess Complex syndrome	Huang Lian E Jiao Tang and Jiao Tai Wan	Coptidis Rhizoma, Scutellariae Radix, Paeoniae Radix Alba, Asini Corii Colla, Cinnamomi Cortex	10.3

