**TCM body constitution assessment**
A comprehensive TCM symptom questionnaire will be administered to evaluate changes in symptoms from the TCM perspective. The questionnaire will assess symptoms across four TCM examinations, such as psychiatric symptoms (e.g. anxiety, depression, irritability), somatic symptoms (e.g. headache, dizziness, fatigue), digestive-related symptoms (e.g. appetite, abdominal pain, constipation, diarrhea), and sleep-related symptoms. The questionnaire will also include tongue and facial inspection, and pulse assessment. Each symptom will be rated by a registered Chinese medicine practitioner based on how often the participant experienced the symptoms over the past 2 weeks on a 4-point scale from 0 (not at all) to 3 (nearly every day).e)

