**Adverse events (AEs)**
All participants will be instructed to report any unexpected symptoms or health issues that arise during the study. Adverse events (AEs) will be categorized by severity - mild, moderate, severe, and undesirable (including life-threatening, disabling, or fatal), and assessed for whether they are related to the intervention. A registered Chinese medicine practitioner will document any adverse events at each TCM body constitution assessment. Participants will be encouraged to contact the research team immediately if any undesirable adverse events occur between scheduled visits. Standard operating procedures will be implemented to manage adverse events:1)Mild AEs potentially related to the intervention: The drug dosage may be reduced by half, with a follow-up assessment scheduled three days later by a registered Chinese medicine practitioner. If symptoms improve, participants may continue with the reduced dosage, with a possible return to the full dosage based on clinical judgment. If symptoms persist or worsen, the medication will be discontinued.2)Moderate AEs potentially linked to the intervention: The medication will be immediately stopped, and a follow-up assessment will occur after three days. If symptoms improve, a reduced dosage may be recommended, with consideration for returning to the full dosage based on clinical judgment. If symptoms do not improve or worsen, the medication will be discontinued.3)Severe AEs require immediate discontinuation of the drug. Reintroduction at full dosage will only be considered if the events are determined to be unlikely related to the intervention and once symptoms have fully resolved.All details of each adverse event will be recorded, including the nature (intervention-related or not), severity, duration, frequency, and any subsequent actions taken.

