### 2.13 Data collection

Following the provision of informed consent during the first visit to the clinic, all participants will complete a validated questionnaire as a baseline assessment. This will be followed by a structured interview to collect basic demographics of each participant, including date of birth, gender, education, employment status, income, household size, and personal habits such as caffeine intake, alcohol consumption, smoking, and exercise routines. Additionally, medical history and any concurrent treatments will be documented. Afterward, participants will undergo a TCM body constitution assessment, during which a Chinese medicine practitioner will prescribe the CHM. At different stages during the intervention period, participants will be required to complete validated questionnaires online and participate in tele-consultations for TCM body constitution assessments (see
Table 3 and
Figure 3). After completing all interventions, participants will be invited to finish a final assessment at the clinic. A follow-up assessment will take place 6 or 12 weeks after the intervention via tele-consultation. To promote participant retention and ensure complete follow-up, participants in Level 1 will be contacted bi-weekly, and those in Level 2 and 3 will be contacted weekly by phone. One day prior to the face-to-face consultation, we will send participants a message reminder of the appointment date and time. Four attempts will be made on two different days to contact each participant.

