### 2.14 Data management

All study data will exclusively be entered electronically within the REDCap system (v14.1.2). Data quality is ensured within the REDCap platform through an integrated script and multiple measures to guarantee data completeness. The extent of actions that each user can undertake is restricted by the rights associated with their respective accounts. To protect participant privacy, sensitive information such as names and phone numbers will be separated from experimental data and securely maintained by designated research personnel. Experimental data will be transferred to an excel spreadsheet, where participants will be de-identified using a coding system. Each code will follow this format: “project name, treatment level (I, II, III), and participant identification code.” A unique three-digit number will be assigned to each participant. For example, data from the first participant in the level 1 treatment group will be labeled as JCI001. All study data will be stored on password-protected computers at Hong Kong Baptist University to ensure security and confidentiality. Access to the data will be restricted to project research personnel and the data monitoring committee. Biological samples obtained from participants will be stored in research center, School of Chinese Medicine, Hong Kong Baptist University for 7 years.

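### The blinding claimed for the clinician-rated TCM body constitution assessment conflicts with the herbs being prescribed during that assessment

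*Protocol article*

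**What the plan says.** Section 2.12 (Blinding) sets up two groups of staff. Of the first it says: "The research personnel responsible for delivering the CHM intervention cannot be blinded either". The second group carries out the TCM body constitution assessment and the objective measurements. That work "will be conducted by research personnel who are blinded to both the study design and participant group allocation", and the section adds: "These assessors will have no role in delivering the intervention". Participants are also told not to reveal their allocation at these assessments. The section presents all this as a measure against bias in a trial whose participants are not blinded.

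Other sections describe the TCM assessment itself:

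- Section 2.13 (Data collection), on the first clinic visit: "participants will undergo a TCM body constitution assessment, during which a Chinese medicine practitioner will prescribe the CHM".
- Section 2.6 (TCM body constitution assessment), on who scores it: "Each symptom will be rated by a registered Chinese medicine practitioner".
- Section 2.5.2 (Level 2), on how treatment is chosen: "A Chinese medicine practitioner will prescribe the herbal formula based on the participant’s TCM syndrome".
- Section 2.6 (Adverse events): "A registered Chinese medicine practitioner will document any adverse events at each TCM body constitution assessment".

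Table 3 (section 2.7) lists the TCM assessment at all nine time points and adverse events at three of them, the assessments immediately after each level.

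**The concern.** A clinician who prescribes the herbs knows that the participant is being treated and takes part in delivering the treatment. If that clinician also rates the TCM symptoms, the rating is neither blinded nor independent of delivery, whatever section 2.12 says.

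What is at stake is how the result may be described. The primary outcomes (PHQ-9, GAD-7, ISI) are questionnaires filled in by participants who know their treatment. The TCM score is the one outcome that section 2.12 calls clinician-rated, so a statement that its raters were blinded would give it more evidential weight than the self-reports. If the statement is wrong for some or all visits, the trial report could present an open rating as blinded evidence.

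**Working it through.** No arithmetic applies. The check sets the sections side by side and asks, for each kind of TCM assessment in Table 3, whether the claim in section 2.12 can hold.

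**1. The first-visit assessment.** Section 2.13 places prescribing inside the assessment. Section 2.12 says that staff who deliver CHM are unblinded, and that TCM assessors are blinded and do not deliver. Prescribing is part of delivery. A practitioner who does both falls into both groups, which section 2.12 treats as separate. The contradiction is direct.

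**2. Could examining and prescribing be split between two people?** The text gives no sign of it. Section 2.6 has the symptoms rated by a registered Chinese medicine practitioner. Section 2.5.2 makes the Level 2 formula depend on the TCM syndrome, judged by the practitioner from the patient's symptoms, signs and constitution. The examination therefore feeds the prescription. No section names a rater distinct from the prescriber.

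**3. Baseline assessments at a step-up to Level 2 or Level 3.** Table 3 lists a TCM assessment at the baseline of each level. A participant who steps up needs a new prescription: a Level 2 formula chosen by syndrome, or a personalised Level 3 formula. It is a reasonable inference that this happens at the same assessment, but section 2.13 states it only for the first visit.

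**4. Assessments immediately after each level (three columns).** Section 2.13 mentions no prescribing here. However, section 2.6 has a practitioner document adverse events at each TCM assessment, and Table 3 ticks adverse events at exactly these three columns, where the post-treatment TCM score is also taken. Section 2.6 requires the record to include whether the event is related to the intervention and what action followed. Someone who completes that record can hardly stay unaware that the participant has taken the herbs. This makes blinding doubtful but does not disprove it: section 2.6 does not say who judges causality, or that the person recording events is the rater.

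**5. Follow-up assessments (6 or 12 weeks later, three columns).** These are tele-consultations. No prescribing is described, and Table 3 does not tick adverse events, although the wording of section 2.6 covers every TCM assessment. The documents leave open whether a blinded rater is used.

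**Result.**

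| TCM assessment | Can the claim in section 2.12 hold? |
|---|---|
| First visit | No, contradicted by section 2.13 |
| Baseline of a later level | No, if CHM is prescribed there, which is likely but not stated |
| Immediately after a level | Doubtful, because adverse events are recorded there |
| Follow-up | Not settled by the text |

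**The case against.** The strongest reply is that section 2.12 states a clear intention to use separate assessors, and that prescribing is described for the first visit only. Sections 2.6 and 2.13 each speak of a practitioner without saying that it is the same one. A second, blinded practitioner could have done the later ratings, where change is measured. If so, withdrawing the claim outright would make the report wrong. This stands as a reason to ask before deleting. It does not rescue the claim as written, which is made for the TCM assessment without limit to particular visits, names no such rater, and is contradicted at the prescribing visit.

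A second reply is that the matter is small: one secondary outcome, in a trial that already admits unblinded participants. That is right, and it limits the consequence.

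Some stronger readings are tempting, but the documents do not support them:

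- **That the participant code unblinds the records.** Section 2.14 does put the treatment level into the code ("data from the first participant in the level 1 treatment group will be labeled as JCI001"). But it describes the code in the spreadsheet after data transfer and does not say that assessors, device staff or laboratory staff see it. Level follows symptom severity and response. It is not the randomised allocation, which is the order in which districts start. Samples and wearable data are scheduled only at Level 2, so their level label would not vary. Each participant also gets a unique three-digit number, which answers the worry that one person would be counted as two.
- **That adverse-event causality is wrongly called blinded.** Section 2.12 makes no such claim, so there is none to withdraw.

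**Conclusion.** The point holds in a limited form. Sections 2.12 and 2.13 contradict each other for the TCM assessment at which CHM is prescribed. The claim is doubtful immediately after each level and unsettled at follow-up. It rests on two readings: that prescribing counts as delivering the intervention, and that no separate rater exists beyond what the article says. The second may turn out to be wrong, which is why the correction is conditional.

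The effect is confined to one secondary outcome. A reader might infer that all the protection offered in section 2.12 fails, or that all nine TCM time points are shown to be unblinded. Neither follows: the prescribing conflict does not touch the wearable or biological-sample data, and prescribing is stated for the first visit only. A reader might also infer a bias in favour of the intervention. That is possible, but nothing in the documents shows its direction or size.

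**What to change.** Reconcile sections 2.6 (TCM assessment and adverse events), 2.12 and 2.13, according to what was actually done:

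- If no rater separate from the prescribing practitioner was used, withdraw the blinding claim for the TCM assessment and report this secondary outcome as an unblinded rating.
- If one was used, state which visits that rater covered and limit the claim to those visits. Say also whether that rater recorded adverse events, and who judged their relation to the intervention.

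Leave the blinding statement for wearable and biological-sample data as it is.

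The cost is a change of wording, with no new visit or assessor, so it remains possible although recruitment is complete. The price is a less favourable blinding statement for one secondary outcome.

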### 2.13 Data collection

Following the provision of informed consent during the first visit to the clinic, all participants will complete a validated questionnaire as a baseline assessment. This will be followed by a structured interview to collect basic demographics of each participant, including date of birth, gender, education, employment status, income, household size, and personal habits such as caffeine intake, alcohol consumption, smoking, and exercise routines. Additionally, medical history and any concurrent treatments will be documented. Afterward, participants will undergo a TCM body constitution assessment, during which a Chinese medicine practitioner will prescribe the CHM. At different stages during the intervention period, participants will be required to complete validated questionnaires online and participate in tele-consultations for TCM body constitution assessments (see
Table 3 and
Figure 3). After completing all interventions, participants will be invited to finish a final assessment at the clinic. A follow-up assessment will take place 6 or 12 weeks after the intervention via tele-consultation. To promote participant retention and ensure complete follow-up, participants in Level 1 will be contacted bi-weekly, and those in Level 2 and 3 will be contacted weekly by phone. One day prior to the face-to-face consultation, we will send participants a message reminder of the appointment date and time. Four attempts will be made on two different days to contact each participant.

### 2.14 Data management

All study data will exclusively be entered electronically within the REDCap system (v14.1.2). Data quality is ensured within the REDCap platform through an integrated script and multiple measures to guarantee data completeness. The extent of actions that each user can undertake is restricted by the rights associated with their respective accounts. To protect participant privacy, sensitive information such as names and phone numbers will be separated from experimental data and securely maintained by designated research personnel. Experimental data will be transferred to an excel spreadsheet, where participants will be de-identified using a coding system. Each code will follow this format: “project name, treatment level (I, II, III), and participant identification code.” A unique three-digit number will be assigned to each participant. For example, data from the first participant in the level 1 treatment group will be labeled as JCI001. All study data will be stored on password-protected computers at Hong Kong Baptist University to ensure security and confidentiality. Access to the data will be restricted to project research personnel and the data monitoring committee. Biological samples obtained from participants will be stored in research center, School of Chinese Medicine, Hong Kong Baptist University for 7 years.

### 2.15 Statistical methods

Data will be presented as mean (standard deviation) or frequency (percentage). The Hussey-Hughes model will be utilized for data analysis, where linear mixed models will be used for continuous outcomes, and generalized estimating equations will be used for categorical outcomes. Pairwise comparisons will be performed using linear contrast. Statistical significance will be considered at p < 0.05. The Holm procedure will be applied to address multiplicity. All statistical analyses will be performed using SAS OnDemand for Academics. All outcomes will be statistically analyzed according to the intention-to-treat principle and the per-protocol population separately.

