**Methods:**

This study will be a multicenter, pragmatic stepped-wedge cluster randomized trial. Districts will be randomized to receive the CHM intervention sequentially in four steps based on a computer-generated number, while control districts remain unexposed until their respective intervention phase. The intervention consists of a three-level stepped-care approach: Level 1 involves herbal tisane for mild symptoms, Level 2 offers standardized CHM for moderate symptoms or non-responders to Level 1, and Level 3 combines personalized CHM with psychotherapy for those not improved by Level 2. Symptom severity will be assessed using validated scales, Patient Health Questionnaire-9 for depression, Generalized Anxiety Disorder-7 for anxiety, and Insomnia Severity Index for insomnia, with primary outcomes measured at baseline, post-intervention, and follow-up. The study was approved by the Hong Kong Baptist University Research Ethics Committee (Approval No.: REC/22-23/0709).

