^ The stepped-wedge design not only facilitates continuous data collection at each intervention phase but also addresses ethical considerations by ensuring that all participants eventually receive the presumed beneficial intervention.
^
36
^ Additionally, this design allows for effective resource management when simultaneous intervention delivery is unfeasible and provides substantial analytical benefits by enabling participants to serve as their own controls, thus enhancing the ability to assess the impact of time on intervention efficacy.
^
36
^ Despite these benefits, the stepped-wedge design has not yet been applied to test the effectiveness of a stepped-care CHM intervention for depression, anxiety and insomnia.

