**Level 1: Herbal Tisane**

The Level 1 intervention, utilizing a low-intensity tisane including four herbs, is designed for participants with mild symptoms of depression, anxiety, and insomnia, defined by a PHQ-9 score ranging from 5 to 9, a GAD-7 score from 5 to 9, or an ISI score from 8 to 14. A Chinese medicine practitioner will prescribe the herbal tisane based on the participant’s main complaints. The Level 1 program includes three types of herbal tisanes for depression, anxiety, and insomnia respectively. Details of these tisanes are listed in
Table 1. The level 1 intervention will last for 6 weeks, where participants will be instructed to take the tisane twice daily. Upon completion of the six-week intervention, participants whose main complaints escalate to moderate level will be stepped up to receive the level 2 intervention, while other participants who present with mild/minimal symptoms will be followed up for another 6 weeks to examine the short-term effects of herbal tisane intervention.

**Table 1. T1:** The composition of the herbal tisane (Level 1 intervention).

	Latin Pharmaceutical Name	Chinese name	g/sachet
Depression Tisane	Curcumae Radix	Yujin	2
	Paeoniae Radix Alba	Baishao	3
	Fructus Tritici Levis	Fuxiaomai	4
	Acanthopanacis Senticosi Radix et Rhizoma Sue Caulis	Ciwujia	3
Anxiety Tisane	Nelumbinis Plumula	Lianzixin	0.3
	Paeoniae Radix Alba	Baishao	2
	Margaritifera Concha	Zhenzhumu	5
	Fructus Tritici Levis	Fuxiaomai	4
Insomnia Tisane	Coptidis Rhizoma	Huanglian	0.6
	Cinnamomi Cortex	Rougui	0.3
	Margaritifera Concha	Zhenzhumu	5
	Poria cum Radix Pini	Fushen	3

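### Section 2.15 fixes a basic Hussey-Hughes model with no participant effect and one treatment term, although the same people are scored before, at the end of and after treatment

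*Protocol article*

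**What the plan says.** Section 2.15 of the protocol article names the analysis: "The Hussey-Hughes model will be utilized for data analysis, where linear mixed models will be used for continuous outcomes". It adds no participant effect and no term separating time points after treatment starts. The same paragraph plans pairwise comparisons by linear contrast.

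The Abstract describes the primary outcomes as taken repeatedly, "with primary outcomes measured at baseline, post-intervention, and follow-up". Table 3 lists PHQ-9, GAD-7 and ISI at three points for each level: baseline, immediately after treatment, and 6 weeks (Levels 1 and 2) or 12 weeks (Level 3) later.

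On timing, Section 2.10 says "All 18 districts will receive no interventions in the first 4 weeks", and then that "this procedure continues at 4-week intervals, until all 18 districts cross over to the intervention phase". For Level 1, Section 2.5.2 says "The level 1 intervention will last for 6 weeks". Level 2 lasts equally long. Participants who are not stepped up from these levels are then observed for a further 6 weeks.

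Section 1.1, arguing for stepped-wedge designs in general, credits them with "enabling participants to serve as their own controls".

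**The concern.** The standard Hussey-Hughes model was written for clusters observed in successive periods. It treats two scores from one person as no more alike than scores from two people in the same district. With three scores per person that is false, so the standard error it reports is not the sampling error of its estimate, and within-person information goes unused.

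The single treatment term is the more serious part, because it affects what is estimated. A score at the end of treatment and a score weeks after treatment stopped carry the same code. If the effect persists unchanged, this does no harm. If it fades, the one reported number is a weighted mixture, with weights set by the visit calendar and the variance components rather than by a clinical question. The primary analysis would then have no defined time point. One coefficient also offers no pair of treatment states to contrast, so the pairwise comparisons promised in the same paragraph have no place in the named model.

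**Working it through.** **Inputs from the article.** 18 randomized districts; 4-week steps after 4 unexposed weeks; four steps; 6-week course and 6-week follow-up (Levels 1 and 2); d = 0.2, two-sided 0.05 and ICC 0.01 (Section 2.8). Section 2.8 computes 1 + (65 − 1) × 0.01 = 1.64, then 260 × 1.64 = 426.4, stated as 428, and 428/0.7 = 611.4, stated as 612. This reproduces. 428/18 = 23.8, so I use 24 people per district.

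**Assumptions.** The article gives no within-person correlation ρ, so I take 0.3 to 0.7. Districts are split 5/5/4/4. Total SD is 1. District effects are either constant over periods or have a between-period correlation of 0.8. Everyone is scored at baseline, 6 weeks and 12 weeks after crossover; step-ups and dropout are ignored. The calendar period of the baseline is not given, so two cases are run: the period that opens at crossover, and the period before it.

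**Visit calendar.** Crossovers fall at weeks 4, 8, 12 and 16. End-of-treatment scores (+6) fall at weeks 10, 14, 18 and 22. Follow-up scores (+12) fall at weeks 16, 20, 24 and 28, none before the last crossover.

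**Formulas.** Named model: score = period + θ × treated + district + error, with working variances 0.01 and 0.99. True variances: district 0.01, participant ρ − 0.01, residual 1 − ρ. With W the inverse working covariance, V the true covariance and A = ΣX′WX:
- reported variance of θ: from A⁻¹
- actual variance: from A⁻¹(ΣX′WVWX)A⁻¹
- type I error = 2Φ(−1.96 × SE/SD)
- power = Φ((0.2 − 1.96 × SE)/SD)

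**Standard error and power (district effect constant over periods).**

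| Baseline in | ρ | Reported SE | Actual SD | Ratio | Type I | Power, named model | Power, participant intercept |
|---|---|---|---|---|---|---|---|
| crossover period | 0.3 | 0.0795 | 0.0741 | 1.07 | 3.5% | 0.72 | 0.79 |
| | 0.5 | 0.0795 | 0.0702 | 1.13 | 2.6% | 0.74 | 0.87 |
| | 0.7 | 0.0795 | 0.0660 | 1.20 | 1.8% | 0.75 | 0.97 |
| period before | 0.3 | 0.1053 | 0.1002 | 1.05 | 3.9% | 0.47 | 0.54 |
| | 0.5 | 0.1053 | 0.0964 | 1.09 | 3.2% | 0.47 | 0.64 |
| | 0.7 | 0.1053 | 0.0926 | 1.14 | 2.6% | 0.47 | 0.81 |

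With between-period correlation 0.8, the lowest ratio is 1.04 (type I error 4.1%), and the lowest participant-intercept powers are 0.77 and 0.53.

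**Pooling.** Set the true effect to 1 at the end of treatment and 0 at follow-up. The expected single coefficient, A⁻¹ΣX′Wμ, is 0.91 with baseline in the crossover period and 1.20 with baseline in the period before. A true mixture of one and zero is thus reported as roughly the full effect or more, with no sign of the fade.

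**Separate terms.** With baseline in the period before crossover, the end-of-treatment term has SE 0.107. Power is Φ(0.2/0.107 − 1.96) = Φ(−0.09) = 0.46, against 0.47 for the named model.

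**Limit.** The working ICC was held at 0.01. A fit that re-estimates it would assign some participant variance to districts. That widens the reported standard error further and raises the pooled multiple, which in the first calendar can land near 1 by coincidence.

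**The case against.** The best defence is that Section 2.15 is one paragraph of an article. Lists of random effects and degrees-of-freedom methods usually sit in the analysis plan, and the planned pairwise contrasts hint that a richer model is meant. This stands in part: an extended model may exist. But the text does not merely omit detail. It names a specific model whose standard form conflicts with the visit schedule and with the contrasts in the same paragraph. A later plan that departed from it would have to say so.

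Four stronger readings are tempting and are not supported:
- **False positives.** In every scenario above, omitting the participant effect makes the test conservative. It costs power and does not create spurious findings.
- **Dilution because a 6-week course outlasts a 4-week step.** The steps do run as "this procedure continues at 4-week intervals", but Table 3 has no mid-course score, so partly treated scores do not enter the analysis as scheduled.
- **Inflated type I error from generalized estimating equations on 18 districts.** The article names no variance estimator, and the primary outcomes are scale scores assigned to mixed models.
- **A broken promise to study effects over time.** The passage about "enabling participants to serve as their own controls, thus enhancing the ability to assess the impact of time on intervention efficacy" is general design rationale. The objective in Section 1.2 is effectiveness, and Section 2.5.1 speaks of clusters as their own comparators.

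It is also fair to say that the magnitudes depend on an unstated calendar. Power differs more between the two calendars than the standard-error ratio does.

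**Conclusion.** The concern holds as a badly fixed choice of primary model. Following Section 2.15 as written gives a standard error about 4 to 20% too wide, type I error about 2 to 4%, and less power than a participant intercept would give for the same single term (0.72–0.75 against 0.77–0.97, or 0.47 against 0.53–0.81, by calendar). These figures rest on 18 × 24 people, ICC 0.01, within-person correlation 0.3 to 0.7, a complete cohort and two assumed baseline calendars. Unbalanced visits could change their size.

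The weightier defect is the single treatment term. Its estimate has no defined time point once the effect changes after treatment stops, and the planned contrasts cannot be formed from it. A reader might infer that the full repair restores the lost power. It need not: with separate terms, one calendar gave 0.46. The case for change is a valid standard error and an interpretable estimate.

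**What to change.** In Section 2.15, replace the basic model for continuous outcomes with a linear mixed model that has:
- fixed calendar-period effects;
- random intercepts for district, district-by-period and participant;
- separate terms for end of treatment and follow-up.

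Name which contrast is primary. State how scores of participants who move up a level are coded, and tie the pairwise comparisons to these terms. A small-sample correction for the generalized estimating equations with 18 districts is an optional addition.

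The cost is protocol or analysis-plan wording and a few lines of SAS, with no new data. The downside is that separating the two terms can reduce precision on the primary contrast, so the amendment should claim no power gain. Recruitment is complete and data collection was due to end in July 2025, so the change should be dated and fixed before outcome data are analysed. A later switch of model would look data-driven.
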